## Abstract

**Background:**

It is estimated that type 2 diabetes (T2D) impacts an estimated 5.3 million Canadians, despite the condition being largely preventable. Laboratory-based diabetes prevention programs (DPPs) have limited effectiveness when translated into community settings due to their low-quality delivery and inability to reach people in the community most in need. To date, no community-based DPPs have been implemented nationwide across Canada. Small Steps for Big Changes (SSBC) is a diet and physical activity counseling intervention that significantly reduces the risk of developing T2D and has been designed for feasible delivery by community-dwelling peers. To ensure maximum public health impact, SSBC must be optimally implemented, demonstrate effectiveness for diverse groups, and be sustainable over time.

**Objective:**

This project aims to adapt SSBC and evaluate the implementation, effectiveness, and sustainability of SSBC in diverse urban communities across Canada.

**Methods:**

A hybrid type 2 implementation-effectiveness study design using multiple and mixed methods will be used to evaluate the implementation and effectiveness of SSBC over 6 years in partnership with 11 regional Young Men’s Christian Associations across 8 provinces in Canada. Beginning in 2024, we will (1) adapt and implement SSBC in diverse urban cities across Canada; (2) examine the implementation (including implementation strategies), effectiveness, and cost-effectiveness of SSBC (2024-2028); and (3) determine the sustainability of SSBC at each delivery location (2028-2029). Data will be collected from SSBC clients, coaches, site leads, and senior leadership municipality partners. The project will be overseen by an advisory group and 3 committees focused on sex, gender, and inclusivity; program evaluation; and diabetes prevention engagement. This study has received ethical approval from the University of British Columbia Clinical Research Ethics Board (H23-01930).

**Results:**

Funding for this project began in October 2022, and Institutional Review Board approval was obtained in October 2023. Program implementation within each region is occurring in a phased approach, with partners beginning program delivery in one site (2024-2025) before expanding to any additional locations (2025-2027). Program enrollment occurs continuously during the implementation phase across all sites. From 2024-2025, a total of 13 delivery sites began program delivery, 722 participants have enrolled in the program, and 406 have begun the program (153/342, 44.7% non-Western or Eastern European; 80/345, 23.2% men or 82/347, 23.6% male). An additional 13 sites have confirmed they will launch the program in 2026.

**Conclusions:**

This study will demonstrate that SSBC can be scaled up nationwide to effectively and equitably reduce the Canadian population-level risk of T2D. This work will determine best practice implementation determinants, outcomes, and strategies critical for sustaining DPP implementation across Canada and beyond. Project findings will be shared with municipality partners and will be copresented with partners and SSBC clients to community organizations, local interested parties, and academics.

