#### Objective 2b: Examine the Effectiveness of SSBC

All clients will complete in-person measurements (weight and waist circumference) at baseline, 12-, and 24-month post program. At locations with an appropriate space (ie, walking track), cardiorespiratory fitness will also be assessed via a 6-minute walk test [79]. In addition, all clients will complete surveys at baseline, session 6, 12, and 24 months post program via REDCap (Research Electronic Data Capture). Surveys will assess self-reported T2D status (12- and 24-months only [80,81]), moderate-to-vigorous PA, dietary intake, and health-related quality of life (EQ-5D-5L) [82]. Table 3 outlines the measures that will be used in the evaluation of SSBC effectiveness. Using an equity-focused lens, a prospective cohort subsample of clients (n=1285) will be followed across 24 months to evaluate the differential impact of SSBC on T2D status, assessed by change in HbA_1c_, in addition to self-reported T2D status. All effectiveness outcomes will be analyzed using descriptive statistics. Hierarchical multivariable regression models will be used to assess the impact of SSBC on effectiveness outcomes, adjusting for potential confounders and accounting for within-subject and within-site clustering. Covariates (ie, sex, gender, and ethnicity) will be included to adjust for within-subject and within-site correlations. A sensitivity analysis using missing data imputation will be conducted to evaluate the potential impact of nonadherence on study outcomes. Data will be disaggregated to examine differences in effectiveness by ethnicity, socioeconomic status, municipality, sex, and gender within and between sites. For the subsample, a multilevel binary logistic regression will be used to examine differences in sociodemographic factors between those who do and do not experience a clinically significant reduction in HbA_1c_ at 24 months.

**Table 3 table3:** Overview of effectiveness measures and associated time points.

		Eligibility	Baseline measurement	Postprogram measurement	Follow-up measurements	
Measure		Online intake survey	Baseline on session 1	After session 6	12-month follow-up	24-month follow-up
Age		✓				
Current T2D^a^ diagnosis		✓				
Prediabetes diagnosis or ADA^b^ diabetes risk score		✓				

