#### Recruitment and Consent

##### SSBC Clients

Recruitment strategies will vary across delivery sites, based on the local connections previously or newly established by the research team and delivery team. A series of generic recruitment materials (eg, posters, pamphlets, or social media posts) and potential recruitment pathways (eg, health assessment days and physician referrals) have been generated by the research team and will be shared with all delivery sites. These recruitment strategies will be included in the implementation strategies’ blueprint and toolkit. Each site will tailor their recruitment plan to the local contextual needs with support from the research team.

Interested or referred individuals will complete an eligibility survey to determine their eligibility for SSBC. Individuals are eligible for SSBC if they are 18 years of age or older, able to read and speak English, and meet one of the following criteria: (1) have been diagnosed with prediabetes by a physician, (2) have an HbA_1c_ of 5.7%-6.4%, (3) have an American Diabetes Association risk assessment score indicating high risk (≥5), or (4) have achieved T2D remission (have an HbA_1c_ of <6.5%) without any diabetes-related medications for a minimum of 3 months. Eligible individuals will be directed to an online consent form. Following completion, individuals will be scheduled for their first SSBC session at their local YMCA implementation site.

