## Results

Program implementation within each region is occurring in a phased approach, with partners beginning program delivery in 1 site (2024-2025) before expanding to any additional locations (2025-2027). Program enrollment occurs continuously during the implementation phase across all sites. From May 2024 to November 2025, a total of 13 delivery sites began program delivery (1 regional YMCA decided to launch in 3 sites at once), 722 participants have enrolled in the program, and 406 have begun the program (153/342, 44.7% non-Western or Eastern European, 17/342, 5% of whom report identifying as Indigenous; 80/345, 23.2% men or 82/347, 23.6% male). Further, 334 participants have expressed interest in the substudy, of which 89 have had their first blood draw (19/89, 21.8% identify as a visible minority; 4/89, 5.3% indigenous; 16/82, 19.5% men or 16/81, 19.8% male). An additional 13 sites have confirmed they will launch the program in 2026.

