## Discussion

### Principal Findings

This study will provide evidence that SSBC can be scaled up nationwide across community settings to equitably and effectively reduce population-level risk of T2D. Nationwide uptake of DPPs has been previously hindered by the absence of evidence-informed implementation plans tailored to local contexts [38]. This project will identify which implementation strategies work best for whom, where, and how, deepening our understanding of how to translate SSBC to multiple contexts. We move beyond a one-size-fits-all strategy to apply evidence-based implementation principles that will result in equitable program implementation for diverse and priority populations across Canada. This protocol paper documents our key objectives and associated methods for other implementation scientists outside of the realm of T2D prevention to consider when planning to implement evidence-based interventions at scale.

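### With every client receiving SSBC and no comparison group described, the planned regression can estimate change among participants but not an SSBC effect or a reduction in population-level T2D risk

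*Protocol article*

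**What the plan says.** The Abstract's Conclusions state: "This study will demonstrate that SSBC can be scaled up nationwide to effectively and equitably reduce the Canadian population-level risk of T2D". The Discussion, under Principal Findings, says it slightly more softly: "This study will provide evidence that SSBC can be scaled up nationwide across community settings to equitably and effectively reduce population-level risk of T2D".

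The analysis meant to support this is in Objective 2b: "Hierarchical multivariable regression models will be used to assess the impact of SSBC on effectiveness outcomes, adjusting for potential confounders". The same paragraph names the covariates: "Covariates (ie, sex, gender, and ethnicity) will be included to adjust for within-subject and within-site correlations". It also plans to break effectiveness down by ethnicity, socioeconomic status, municipality, sex and gender, within and between sites. In the HbA1c subsample (n=1285), a multilevel logistic model compares clients who do and do not reach a clinically significant HbA1c reduction at 24 months.

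On the source of the data, the Abstract's Methods say: "Data will be collected from SSBC clients, coaches, site leads, and senior leadership municipality partners". On what happens after eligibility and consent, the SSBC Clients section says: "Following completion, individuals will be scheduled for their first SSBC session at their local YMCA implementation site". Under Results: "Program enrollment occurs continuously during the implementation phase across all sites". Strengths and Limitations does not mention the absence of a comparison group.

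**The concern.** A reduction in risk is a comparison with the risk that would have applied without the programme. Here everyone observed receives the programme, so that second quantity is not observed, and the article does not say where it would come from.

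The gap is sharpest for T2D status. Apart from entrants in remission, clients start without T2D, so the cumulative proportion with T2D can only rise from near zero. Calling the 24-month figure a reduction has no meaning until an untreated rate is set beside it. For HbA1c, weight and activity a before-after change does exist, but it mixes the programme with everything else that happens to a self-selected or referred at-risk group over two years.

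At stake is whether a descriptive result is later read as a programme effect. The Methods sentence on impact and the two conclusions would both allow that reading.

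**Working it through.** **1. Is there a comparison group anywhere in the article?**
- Outcome measures (Table 3) are taken on SSBC clients only, at baseline, after session 6, and at 12 and 24 months.
- Table 1 counts people who show interest but do not sign up. No outcomes are planned for them.
- Sites start in phases, but clients are enrolled only to receive the programme. No pre-launch observations are described.
- The figure of 70% progressing in 10 years appears in the Introduction as background, not as a benchmark.
- Objective 2c speaks of incremental costs and effects but names no comparator.

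**2. What can a regression separate?** The article does not write out its model, so take the two simplest forms.
- Between clients: columns for intercept, SSBC and sex. SSBC equals 1 for everyone and duplicates the intercept. The rank is 2 of 3.
- Before versus after: columns for intercept, exposed and time. Exposed is 0 at baseline and 1 afterwards, so it duplicates time. The rank is 2 of 3.

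In words, mean change from baseline = effect of SSBC + change that would have occurred anyway. Only the sum is estimable. Extra follow-up visits do not help without an assumed shape for the untreated course, because each client has one pre-programme measurement. Staggered entry might inform a calendar trend if later entrants were exchangeable with earlier ones. That is not planned, and it would leave natural progression and regression to the mean untouched, since both run on time since entry.

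Sex, gender and ethnicity are treated as fixed client attributes. As main effects in a linear model they cancel from a within-client difference. As interactions with time they describe who changes more. Neither supplies the missing term.

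**3. Illustration of size.** The article gives n=1285 and 70% in 10 years. Everything else here is an assumption.
- 24-month risk from 70% in 10 years: constant hazard, 1 − 0.3^0.2 = 21.4%; linear, 70% × 2/10 = 14%.
- Assumed incidence among clients: 8%. Standard error = √(0.08 × 0.92 / 1285) = 0.0076; 95% CI 6.5% to 9.5%, taking full follow-up and no clustering.
- Relative change = 0.08 / untreated risk − 1:

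| Assumed untreated 24-month risk | Relative change at 8% |
|---|---|
| 21.4% | −63% |
| 14% | −43% |
| 10% | −20% |
| 6% | +33% |
| 4% | +100% |

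The spread comes from the unobserved quantity, not from sampling error, so a larger n would not narrow it. The article gives no inputs from which n=1285 could be reproduced. That is not counted here.

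**4. Regression to the mean.** A simulation with no true change selected people on a first HbA1c of 5.7% to 6.4%. It assumed population means of 5.6 or 5.9, between-person SD 0.30 to 0.35 and within-person SD 0.15 to 0.20. Mean change at retest was −0.02 to −0.10 points, and 11% to 29% fell below 5.7%. This applies only to clients entering on a measured HbA1c, one of four entry routes. It also treats the qualifying value as the baseline. Where the substudy's own baseline sample follows an earlier qualifying test, part of this shift would already have occurred.

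**The case against.** The strongest reply is that Objective 2b does more than compare before with after. It plans contrasts between subgroups, municipalities and sites, and the subsample is there to study differential impact. Client and site characteristics do vary, so covariate adjustment has a proper role in those contrasts. This stands. A reader might infer that the regression can estimate nothing, or that all adjustment should be dropped. The documents do not support that, and the point is limited to the average effect of SSBC as distinct from time.

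Second, the article does not present itself as a controlled trial. Its design is hybrid type 2, its stated aim is to evaluate, and it cites earlier work for efficacy. This also stands, and nothing here requires a control group. It does not rescue the two conclusions, which go beyond evaluating.

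Third, one could add that volunteers at purposively chosen sites cannot support a population statement. The article answers part of this: sites were chosen for diversity, client demographics will be compared with people with prediabetes across Canada, and the substudy oversamples visible minorities and males with six-monthly checks. These steps bear on who is represented, though they supply no untreated risk. Generalisability is therefore not pressed.

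Fourth, the full protocol or analysis plan may hold the covariate list, the model and causal caveats. That is fair for detail. But the article itself states both the conclusion and the regression offered in support, and an analysis plan cannot by itself add an unexposed group that the described data collection lacks.

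**Conclusion.** The point holds in this form: as written, the Abstract and Principal Findings claim a reduction in population-level risk, and Objective 2b claims an adjusted impact of SSBC, that the described design cannot identify. What it can give is change within clients and differences in that change between groups and sites.

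This rests on there being no comparison group, as the article describes it. It does not depend on the illustrative numbers. A reader might take the range from a 63% reduction to a doubling as a forecast of what will be reported. It is not: the article plans no comparison with an untreated rate, and the 8%, the lower benchmark risks and the conversion of the 10-year figure are all assumptions. The range shows only that the direction, not just the size, of an implied effect would depend on a number the study does not collect.

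**What to change.** - **Objective 2b:** state the estimand as covariate-adjusted within-client change at 12 and 24 months, with subgroup and site differences in that change, plus 24-month cumulative T2D incidence among SSBC starters without T2D at entry. The intake survey already records current T2D diagnosis; say how entrants in remission are counted. Describe the covariates as prognostic or effect-modifying for the overall change, and keep adjustment for the between-group contrasts.
- **Abstract, Conclusions, and Discussion, Principal Findings:** replace the demonstrated or evidenced reduction in population-level risk with before-after change among participants.
- **Strengths and Limitations:** state that the study has a single arm and that change cannot be attributed to SSBC apart from natural progression, regression to the mean, secular trend and other care.
- **Optional:** if a comparison with an untreated progression rate is wanted, prespecify it, label it external and show it over a range. The remedy does not depend on this.

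The cost is wording in four places. No change to data collection is needed, and the planned models can stay. The real price is a less favourable claim.

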**Trial Registration:**

ClinicalTrials.gov NCT06440395; https://clinicaltrials.gov/study/NCT06440395

**International Registered Report Identifier (IRRID):**

DERR1-10.2196/80276

## Introduction

The incidence of type 2 diabetes (T2D) is continuing to rise worldwide [1,2] despite overwhelming evidence that this chronic disease is largely preventable [3-5]. As the fastest-growing chronic condition, T2D impacts an estimated 5.3 million Canadians [6], with estimated annual treatment costs of CAD $30 billion (a currency exchange rate of CAD $1=US $0.71 was applicable) [7]. An additional 6 million Canadians [6] live with prediabetes, a clinical condition recognized by the World Health Organization that precedes T2D. Further, 70% of individuals with prediabetes are estimated to progress to T2D in the next 10 years [8]. Rates of T2D are higher in areas with lower household income and education level, higher levels of food insecurity, unemployment, immigrant status, and among individuals of African, South Asian, and Indigenous origins [7-10]. Racial, sex, and gender-based health inequities in accessing care exacerbate these barriers [11-16]. Preventing the progression of prediabetes to T2D and addressing health inequities is a public health priority in Canada [17].

T2D prevention programs (diabetes prevention program [DPPs]) have been shown to reduce the progression of prediabetes to T2D in diverse populations and geographic regions of the world. Three landmark trials involving more than 4000 individuals with prediabetes demonstrated that increasing physical activity (PA) and inducing modest weight loss through dietary intervention can reduce the risk of developing T2D by between 50% to 60% [18-20]. Notably, diet and PA approaches were twice as efficacious as pharmaceutical interventions [18]. However, translating these highly efficacious DPPs into community settings for public health impact often results in reduced effectiveness [21,22]. This drop in efficacy is often attributed to inequitable access [23,24], poor fidelity [25-29], lack of cultural tailoring [11,30-34], and lack of sustainability plans [30,35-37].

To date, no community-based nationwide DPP has been implemented across Canada. To make a measurable impact on T2D prevention at a population level, potent evidence-based interventions must be implemented effectively at scale. Nationwide uptake of DPPs is hindered by the absence of evidence-informed implementation plans tailored to local contexts [38] and the examination of individual- and between-delivery site differences to understand the impact of context on implementation. Site contextual differences are common, as each community has unique challenges and opportunities that impact implementation, and remain an understudied paradox of implementation efforts [39]. Additionally, equity-based contextual factors, including access and cultural relevance for populations traditionally underserved and racialized against, are pivotal considerations for implementation scale-up [40,41]. It is imperative to disaggregate multisite data and understand how community-, organization-, provider-, and client-level factors contribute to implementation outcomes when organizations deliver the same program in different contexts [41,42]. Implementation studies with a focus on context, and in particular health equity, are needed to compare within and between-site implementation outcomes and determinants [41]. Understanding these contextual factors is also key for identifying methods (implementation strategies) required to enhance the implementation and scale-up of DPPs [43].

Further limiting DPPs from achieving population-level health impact is a failure to prioritize and support the sustainability of these evidence-based programs after they have been implemented. Sustainability, defined as the continued use of program components at sufficient intensity for the sustained achievement of desirable program goals and population outcomes [44], is now considered “one of the most significant translational research problems of our time” [45]. Sustaining evidence-based interventions is imperative to assess long-term health outcomes, inform scale-up of implemented programs, avoid debilitating policy and ethical implications of abandoning funded effective interventions, and maintain community support and trust in research [44]. To maximize the public health impact of evidence-based interventions, it is critical to investigate the factors and processes that influence both implementation and sustainability of these interventions, and the health behaviors and outcomes they produce [44,46]. Adaptability, partnership with organizations delivering the intervention, and commitment from the community have been suggested as key factors in sustaining disease prevention programs [47,48]. The call for sustainable solutions to T2D prevention has yet to be answered [49], with no study to date examining how to sustain evidence-based DPPs in “real-world,” community contexts. Implementing and sustaining evidence-based DPPs has implications for substantially reducing the incidence of T2D in Canada, and beyond, and simultaneously fulfilling an important knowledge gap in implementation science.

Small Steps for Big Changes (SSBC) is an evidence-based DPP, consisting of behavior change techniques for diet and PA modification delivered in six 1-hour sessions. Since development in 2013, SSBC has been systematically scaled up from preliminary efficacy testing in a laboratory setting to real-world effectiveness trials in 1 urban and 5 rural community settings in British Columbia (BC) [37,50-55]. Our research to date has demonstrated that SSBC can be adapted for implementation in community settings, delivered in-person and virtually by “laypersons” with no specialized education or experience [56,57], and results in short- [58], medium- [52,59], and long-term behavior changes [60] ([name] et al, unpublished data, 2025) leading to clinically relevant improvements. Most notably, 41% of clients who participate in SSBC no longer have prediabetes (glycated hemoglobin [HbA_1c_] <5.7%; American Diabetes Association criteria) 1 year post program, with a further 16% on the cusp of no longer being prediabetic with HbA_1c_ levels of 5.7% ([name] et al, unpublished data, 2025).

Nationwide scale-up of SSBC presents a promising public health solution to equitably reach and improve the health of the growing number of Canadians who are at risk of developing T2D. As such, this project aims to evaluate the implementation, effectiveness, and sustainability of SSBC as it is scaled up nationwide across diverse urban communities in Canada. To address this aim, the project has three objectives (Figure 1): (1) To adapt and implement SSBC in diverse urban cities across Canada; (2) to examine the implementation (determinants, outcomes, and strategies), effectiveness, and cost-effectiveness of SSBC; and (3) determine the sustainability (determinants and outcomes) of delivering SSBC in these contextually varied urban locations.

